## Abstract

**Background:** Cultural safety encourages practitioners to examine how their own culture shapes their clinical practice, and to respect their patients’ worldviews. Lack of cultural safety in health care is linked to stigma and discrimination towards culturally diverse patients. Training in cultural safety has considerable challenges. It is an unappealing subject for medical students and requires behavioural changes in their clinical practice. Game jams, collaborative workshops to create and play games, have recently shown effectiveness and engaging potential in university-level education.

**Objective:** The trial aims to determine whether medical student participation in a game jam to design an educational game on cultural safety is more effective than a standard lesson on cultural safety in terms of change in students’ self-reported intended patient-oriented behavior.

**Methods:** A parallel group, two arm, randomised controlled trial with a 1:1 allocation ratio will randomize 340 medical students and 60 medical interns (n=400) at the Faculty of Medicine at *La Sabana* University, Colombia (170 students and 30 medical interns to each arm). The intervention group will participate in an 8-hour game jam comprised of: (i) a preliminary lecture on cultural safety and game design; (ii) a game building session where groups of students will create educational games about cultural safety; and (iii) a play-test session in which students will play and learn from each other’s games. The control group will receive a standard lesson, including a 2-hour lecture on cultural safety, followed by a 6-hour workshop to create posters about cultural safety. Online self-administered 30-item Likert-type questionnaires will assess cultural safety self-reported intended behavior before, immediately after, and six months after the intervention. An intention-to-treat approach will use a t-test including 95% confidence intervals to determine the significance of the effect of the intervention, including within- and between-group comparisons. The qualitative Most Significant Change technique will explore the impact of the intervention on the clinical experience of the students.

**Results:** Study enrollment began in July 2019. 640 students completed the baseline survey and were randomised. Data collection is expected to be complete by July 2020 and results are expected in October 2020.

**Conclusions:** The research will develop participatory methods in game-based learning co-design that might be of relevance to other subjects. Ultimately, it should foster improved cultural safety skills for medical students, improve quality of health services for diverse cultural groups, and contribute to enhanced population health. Game learning may provide an innovative solution to a long-standing and neglected problem in medical education, helping to meet the educational expectations and needs of millennial medical students.

**Trial registration:** ISRCTN registry. The trial registration number is ISRCTN14261595 <http://www.isrctn.com/ISRCTN14261595>

**Keywords:** transformative learning, medical education, cultural safety, participatory research, game jam

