### Eligibility criteria

The inclusion criteria are: (i) being a medical student or medical intern at any level of training and (ii) giving informed consent. The exclusion criterion is not wanting to participate in the study.

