### Recruitment

We will contact the medical students and medical interns using *La Sabana* University’s mailing lists and will e-mail invitations for voluntary participation in the project. For those willing to participate, we will send further information about the project as well as the date and place of the intervention. We will ask interested students to complete the online informed consent and baseline questionnaire one week before the RCT.

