### Allocation

A potential source of bias in our study is a possible imbalance in the level of cultural safety training between the intervention and control groups before the intervention. The reason for this issue is that in Colombia around 40% of the population uses cultural and traditional practices to maintain their health.[28] Therefore, some students will be familiar with traditional health practices, probably making them more likely to embrace the cultural safety approach compared with students not familiar with these practices.

To address this potential bias, we will use stratified randomization by cultural safety score at baseline. Based on the preliminary results of the baseline survey, we will split the group of medical students into two groups: low and high level of cultural safety knowledge. Computerized randomization will allocate the students either to the intervention or control arm and we will use equal allocation between treatment arms. The study coordinator will be responsible for generating the allocation sequence, enrol participants, and assign participants to interventions.

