The instructions will make clear that participants should feel free to write down stories of negative changes or to say that they did not experience any change at all. Only medical students involved in clinical practice and medical interns (third to seventh year of medical school) will be invited to participate in this part of the RCT.

Methods to maximise completeness and quality of data: The study coordinator and facilitators will be physically present while collecting the data at each time point to ensure the completeness of data. Additionally, we will use several validation options to increase the quality of the data: specific number range, specific character range, date validation, email address format, and prompts that alert participants when they enter incomplete or invalid answers.

In this study, the familiarity of millennial medical students with technology and computer-based education supports using Web-based questionnaires, which reputedly decrease social desirability bias.[40] Assured of anonymity, respondents should be less concerned about what others may think about their responses, including peers and professors.[41] Data reliability in Web-based questionnaires is reportedly equal to or better than traditional paper-based approaches.[42] Examples include data on self-reported perceived health status, oral contraceptive use, and smoking and alcohol use. Web-based questionnaires are also faster to complete and typically cheaper than traditional approaches, making them ideal for our research.

Methods for ensuring secure storage of data: SurveyMonkey and Google responses are stored in a worksheet that can only be accessed through an account login. Data transmission uses Secure Sockets Layer to encrypt information during transport. The data storage is as secure as most other systems that store survey information. After downloading the data, we will delete it from SurveyMonkey and Google Forms. We will be responsible for ensuring the data are securely stored for seven years and then destroyed in accordance with CIET guidelines for security, storage, and eventual destruction of data records.[43]

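### The stated 170 students and 30 interns per arm is not secured by eligibility, recruitment or allocation, and the unadjusted primary t-test leaves chance imbalance in training level uncorrected

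*Protocol*

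**What the plan says.** The Abstract states that the trial "will randomize 340 medical students and 60 medical interns (n=400"), and gives the split as "170 students and 30 medical interns to each arm". Neither figure is marked as approximate or expected.

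The Methods sections that would have to deliver these figures say the following:

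- **Eligibility criteria:** the criterion is "being a medical student or medical intern at any level of training", plus consent. There is no quota or cap by level.
- **Recruitment:** using the university mailing lists, the team "will e-mail invitations for voluntary participation in the project". There is no target by level.
- **Allocation:** "we will use stratified randomization by cultural safety score at baseline". The strata are formed as "we will split the group of medical students into two groups: low and high level of cultural safety knowledge", and "we will use equal allocation between treatment arms". Training level is not a factor.
- **Data collection methods:** level of training is among the sociodemographic variables in the first part of the questionnaire. For the narrative component, "Only medical students involved in clinical practice and medical interns (third to seventh year of medical school) will be invited".
- **Methods for analyzing data:** the primary between-group comparison is a t-test. Sociodemographic baseline variables are adjusted for only in the secondary analysis, by logistic regression and the Mantel-Haenszel procedure.

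The Results report 640 people randomised without separating students from interns. Item 17 of the registration data set in the Appendix gives a target sample size of 330.

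**The concern.** An exact per-arm composition reads as a property of the design. A reader of the Abstract would assume either quotas with stratification by student or intern status, or some other restriction on the allocation. The Methods describe neither, so the number of interns enrolled and their division between arms are both uncontrolled.

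Training level has some bearing on the outcomes. The items forming the primary outcome ask what participants think and intend in relation to their own patients, and participants range from first-year students to interns in clinical work. The narrative component is open only from third year on, so level also determines who can contribute to it. If level predicts the primary score, an uneven split adds noise to the arm difference. The planned primary test does not remove that noise, although the variable needed to do so is collected.

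**Working it through.** **1. The plan's own arithmetic.** 340 + 60 = 400 and 170 + 30 = 200 per arm. The figures agree with each other and imply an intern share of 60/400 = 15%.

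**2. Is the total of 60 interns secured?** Study setting gives 956 students and 256 interns, so interns are 256/1,212 = 21.1% of the source population. If volunteers came forward in proportion (an assumption), 400 participants would include 400 × 0.211 ≈ 84 interns. The 60 is therefore a planning figure that recruitment does not enforce.

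**3. Is 30 per arm secured, given 60 interns?** Take N = 400, K = 60 interns and n = 200 per arm, with allocation unrelated to level. The number of interns in one arm is hypergeometric.

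- Mean: nK/N = 200 × 60/400 = 30.
- SD: √[n(K/N)(1 − K/N)(N − n)/(N − 1)] = √[200 × 0.15 × 0.85 × 200/399] = √12.78 = 3.6.
- 2.5% to 97.5% quantiles: 23 to 37.
- P(exactly 30) = 0.111.
- P(27 to 33) = 0.67.
- P(25 or fewer, or 35 or more) = 0.21.

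**4. Does stratifying by score change this?** Assume two score strata of 200. With interns divided 30/30 between the strata, P(exactly 30 per arm) = 0.111. With interns divided 10/50, it is 0.116. The range stays at 23 to 37 in both cases.

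**5. Effect on the primary comparison.** A 37/23 split is a difference in intern share of 14/200 = 0.07. The shift in the arm difference is 0.07 × g, where g is the mean difference between interns and students in SD units. The protocol gives no value for g, so a range is assumed.

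| Assumed g (SD) | Shift (SD) | Shift in score points (SD 4) |
|---|---|---|
| 0.25 | 0.07 × 0.25 = 0.018 | 0.07 |
| 0.5 | 0.07 × 0.5 = 0.035 | 0.14 |
| 1.0 | 0.07 × 1.0 = 0.070 | 0.28 |

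The planned effect in the Sample size section is 26.9 − 25.9 = 1.0 point, or 1.0/4 = 0.25 SD.

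**6. The same check at 640 randomised, assuming 320 per arm.**

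- At a 15% share there are 96 interns, with mean 48 per arm, SD 4.5 and range 39 to 57. The extreme difference in share is 18/320 = 0.056, giving a shift of 0.014 to 0.056 SD over the same range of g.
- At a 21.1% share there are about 135 interns, with range 57 to 78. The extreme difference is 21/320 = 0.066, giving a shift of 0.016 to 0.066 SD.

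**7. What adjustment could gain.** With a 15% intern share, the student–intern contrast explains 0.15 × 0.85 × g² of the outcome variance: 0.008, 0.032 and 0.128 for g = 0.25, 0.5 and 1.0. The variance of the adjusted arm difference falls by about those fractions. This leaves out anything explained by year among students or by the score stratum.

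**The case against.** The strongest reply is that only a parenthesis in the Abstract is at fault. If 60 interns enrol under 1:1 allocation, 30 per arm is the expected number, and the figures can be read that way. Randomisation balances training level in expectation, and the t-test's confidence interval already allows for chance imbalance. The protocol stratifies on the imbalance it names as a worry, prior cultural safety level, and that may capture part of any training effect. It also collects level of training and plans an adjusted secondary analysis.

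Most of this stands, and it limits the point. The reply about secondary adjustment is only partly sufficient. Logistic regression and Mantel-Haenszel work on a categorised outcome and do not return an adjusted mean difference on the primary score, so the primary estimate remains unadjusted.

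A reader might infer several stronger things that the document does not support:

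- **That the arms are in fact unbalanced, or the composition was not delivered.** No split of the 640 is reported. The most that can be said is that it was not secured.
- **That the comparison is biased.** The imbalance is random. The year restriction on the narrative component rests on a characteristic fixed before randomisation and applies to both arms alike, and that analysis is thematic, not numerical.
- **That interns were left out of the strata** because the Allocation section mentions only students. The protocol uses the word loosely for all participants, as in its report of the 640. This deserves clarification but is not evidence of exclusion.
- **That training level is the protocol's key factor.** Nothing in the text says so.

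**Conclusion.** The point holds as a mismatch between the Abstract and the Methods, together with a missed and inexpensive improvement to the primary analysis. It does not show a defective randomisation.

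Under the Abstract's own totals, an exact 30/30 split has about an 11% chance, and a split of 35/25 or worse about 21%. The consequence for the primary result is small. Even at the edge of the 95% range, the shift is about 0.02 to 0.07 SD against a planned 0.25 SD, and somewhat less if 640 were randomised with the same intern share. These sizes rest on an assumed intern–student difference of 0.25 to 1.0 SD and, for the 640, on assumed intern shares and equal arms.

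The precision gained from the student–intern contrast alone would be about 1% to 13% of variance over that range. This is worth having because the covariate is already in the data, but it would not rescue or overturn the trial.

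**What to change.** **Primary analysis (Methods for analyzing data).** Replace the unadjusted between-arm t-test with a linear model (ANCOVA) of the primary score. Its terms would be arm, level of training in three categories (years 1–2, year 3 to pre-internship, interns) and the low/high baseline score stratum used in randomisation. Report the adjusted mean difference with its 95% confidence interval, and keep the unadjusted t-test as a sensitivity analysis. If the model replaces the test one for one, the number of between-arm p values in the Holm procedure does not change. The planned multiple imputation can be combined in the same way.

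**Composition.** Replace the 340/60 and 170/30 figures with the numbers actually randomised by level and arm, or label them as expected. Reconcile them with the 640 in the Results and the 330 in the Appendix. State whether interns were included in the score strata, and report how many in each arm were eligible for the narrative component.

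**Not proposed.** A further stratification factor would serve no purpose now that allocation is complete.

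**Cost.** No new data are needed, provided the baseline item on level of training distinguishes these three categories. The real cost is a change to the primary analysis after randomisation. It has to be documented and dated before the data are analysed, with a statement that no outcome comparison by arm had been seen.

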## Introduction

### Cultural safety training

Although cultural safety is an evolving term and lacks a formal definition,[1] it is often described as a space “that is spiritually, socially, emotionally and physically safe for people; where there is no assault, challenge or denial of their identity, of who they are, and what they need.”(p272)[2] The concept originated in New Zealand to address the disconnect between the type of health care that Indigenous Maori people were receiving and the culturally-congruent care that they were advocating for.[3]

Cultural safety has gradually gained attention because it offers a more comprehensive and respectful way to approach culture, in many settings replacing the current standard, which is cultural competence.[4] Cultural safety is distinct from cultural competence, in that it invites culturally diverse patients and their communities to co-design and evaluate culturally safe health care.[1][5] Recent evidence suggests that cultural safety education is linked to better relationships between culturally diverse patients and clinicians and improved health outcomes.[2]

The Royal College of Physicians and Surgeons of Canada will soon require all medical residency programs to provide mandatory cultural safety training.[6,7] There is, however, little research on how to implement this approach in medical education,[8] and how health professionals acquire cultural safety skills is poorly understood.[9]

There are additional challenges to promoting cultural safety in medical education. Educators might find cultural safety complicated to teach and medical students may perceive it dull.[10]^,^ Contemporary medical training is almost everywhere overloaded, with little space to include an entirely new if very important subject. Millennial medical students – the birth cohort between 1979 and 2000 [11] – have new learning relationships with technology, creativity, and amusement that modern teaching strategies cannot overlook.[12] Finally, cultural safety training goes beyond merely knowledge acquisition; it must promote a *transformative* experience to impact students’ behavior in clinical practice. The theory of transformative learning provides a framework to address these challenges.[13]

### Transformative learning and game co-design

Mezirow describes transformative learning as a process that changes frames of reference, “the structures of assumptions through which we understand our experiences.”(p5)[13] Frames of reference are comprised of habits of mind, which are habitual ways of thinking and acting, and points of view, which are beliefs, values, and attitudes.

Mezirow argues that ethnocentrism, defined as “the predisposition to regard others outside one’s own group as inferior,”(p6)[13] is an example of a habit of mind. Ramsden, the Maori nurse who developed the concept of cultural safety, proposes that confronting ethnocentrism must be the first step in cultural safety training.[3] Transformative learning may be, therefore, suitable to provide cultural safety training to medical students.

Transforming frames of reference requires reflection on the assumptions upon which learners base their habits of mind and points of view.[13] In transformative learning, people become critically reflective of their assumptions through education that is participatory and interactive and through group problem-solving or communicative learning.[14]

*Game jams* provide an environment to foster learning through interacting and communicating with others,[15] an essential aspect of transformative learning. These participatory events allow attendees to create games (digital or board games) in a time-constrained environment.[16] Unlike other educational approaches, game jams could offer a solution to the challenges of cultural safety in medical education by (i) engaging Millennial students through a culture of creativity and learning, play testing, and idea sharing; (ii) supporting a transformative process of learning-by-doing while enhancing creative thinking, problem-solving, communication, and innovation; and (iii) promoting transformative learning in less time, thus offering an alternative to overloaded medical curricula.

Fowler and collaborators recently found that game jam participation could improve computing students' performance.[15] We are not aware, however, of any reported experience using game jams to train medical students. Our primary objective is to determine whether medical student participation in a game jam to design an educational game on cultural safety is more effective than a standard lesson on cultural safety in terms of change in students’ self-reported intended patient-oriented behavior. Our secondary objectives are to: (i) determine the impact of the intervention (game jam) compared with the control (standard lesson on cultural safety) on students’ confidence in their general transcultural skills; and (ii) assess the impact of participation in the game jam through a narrative approach that identifies in their own words the effect of the learning on cultural safety in their clinical practice.

## Methods

### Trial design

A parallel group, two arm randomised controlled trial (RCT) with 1:1 allocation will compare participation in a game jam with a standard lesson on cultural safety. The RCT will answer the question: *Among medical students and interns from La Sabana University, does participating in a game jam for cultural safety training, in comparison to a standard lesson on cultural safety, result in increased change in students and interns’: (a) self-reported intended behavior; (b) confidence in general transcultural skills; and (c) reported change in clinical practice?* Table 1 presents the PICOT components of the research question. This protocol description follows the SPIRIT (Standard Protocol Items: Recommendations for Interventional Trials) 2013 statement[17] (Multimedia Appendix 1: SPIRIT checklist of the study protocol).

Table 1. Population, intervention, contrast, outcome, and timing (PICOT) of the RCT

| **Components** | **Description** |
| --- | --- |
| Population | Undergraduate medical students and medical interns at *La Sabana* University in Colombia |
| Intervention | Game jam aimed at fostering cultural safety in clinical practice |
| Contrast | Standard lecture and workshop on cultural safety |
| Outcome | (i) Cultural safety intended patient-oriented behavior change outcomes from knowledge to action; (ii) Students’ confidence in general transcultural skills; and (iii) Qualitative understanding of the change experienced by participants in their clinical practice |
| Timing | Before the intervention, immediately following the teaching session, and six months post-intervention |

### Study setting

We will conduct the RCT at the Faculty of Medicine at *La Sabana* University in the municipality of Chía, Colombia. Chía is a small town located 15 km from Bogotá, the capital of Colombia. *La Sabana* University is a private higher education institution that has 8,926 undergraduate students; 22% of these students come from a low socioeconomic level, 52% belong to the middle class, and the remaining 26% come from higher socioeconomic backgrounds.[18] Presently, there are 956 students enrolled in medical school and 256 medical interns (n=1,212).[18] At *La Sabana*, the duration of the MD program is seven years. As part of that training, all medical students must undergo a one-and-a-half-year medical internship before graduating.

